##### **2) Blood lipid**

Measures of blood lipid variables include: total cholesterol (TC), triglyceride (TG), low-density lipoprotein cholesterol (LDL-C) and high-density lipoprotein

cholesterol (HDL-C).

Measuring instrument: CardioChek PA Blood Analyzer. Place of Origin: USA

Measuring place: The Physical Fitness Testing Center of Jiaozuo People's Hospital, Jiaozuo City, China. Due to the particularity of blood lipid measurement, the measurement and evaluation will be completed by a qualified nurse.

### **3.7.2 Secondary outcome measures**

#### **1) Flexibility**

Measurement name: Sit and Reach Test

Measuring instrument: WQ-168 sitting body forward bending tester. Place of Origin: China Beijing Weixin Yiao Technology Development Company.

Measuring place: Physical Fitness Testing Center of Tai Chi Sports Center, Jiaozuo City, China. The assessment is conducted by a qualified assessor.

#### **2) Upper limb strength**

Measurement name: Grip strength test

Measuring instrument: Electronic grip strength tester HKD-1881. Place of Origin: Beijing Hongkangda Sports Technology Company produces.

Measuring place: Physical Fitness Testing Center of Tai Chi Sports Center, Jiaozuo City, China. The assessment is conducted by a qualified assessor.

#### **3) Lower limb strength**

Measuring instrument: Wall squat test (Vaegter et al., 2019).

The wall squat test is a simple test of lower-body muscle strength and endurance. The test requires participants to sit while leaning back against the wall. Need flat non-slip floor, smooth wall, and stopwatch.

Measuring place: Physical Fitness Testing Center of Tai Chi Sports Center, Jiaozuo City, China. The assessment is conducted by a qualified assessor.

#### **4) Balance**

Static balance measuring: The Balance Error Scoring System (BESS). A previous research report pointed out that the use of BESS to test static balance has high reliability between measurers (within-class correlation coefficient = .78 to .96), and fairness of validity is good ( $r = .42$  to  $.79$ ) (Riemann et al., 1999), so this method

is used for static balance assessment.

Dynamic balance measuring: The Star Excursion Balance Test (SEBT) (Gribble and Hertel, 2003). Previous research reports pointed out that the use of SEBT to test adult dynamic balance has high reliability between measurers (within-class correlation coefficient = .78 to .96) (Hertel et al., 2000), so this method is used for dynamic balance assessment.

Measuring place: Physical Fitness Testing Center of Tai Chi Sports Center, Jiaozuo City, China. The assessment is conducted by a qualified assessor.

### **5) Aerobic endurance**

Aerobic endurance Measuring: The six-minute walk test (6MWT) (Eden et al., 2018)

Measurement place: Standard 800-meter track of Tai Chi Sports Center in Jiaozuo City, China. The assessment is carried out by qualified assessors.

### **3.7.3 Safety indicators**

The side effects and adverse events that occurred during the study were recorded, and the reasons were analyzed. The incidence of adverse events in each group was used as the evaluation index. The calculation formula of the incidence of adverse events is as follows:

The incidence rate of adverse events % = (number of adverse events/total number of cases in this group) × 100%

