#### **3.2.3 Exit criteria**

- 1) Those who can't insist on training;
- 2) Those who do not practice according to the training requirements;
- 3) Sudden illness or injury occurred during the test and cannot continue to participate in the training;

- 4) Those who voluntarily propose to quit the researcher;
- 5) The control group members practice Tai Chi during the experiment;
- 6) Those who have adverse events and are not suitable to continue practicing.

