### **3.5 Intervention time**

The Bafa Wubu Tai Chi group and the traditional He-style Tai Chi group will receive Tai Chi training 12 weeks, 3 times a week, each course is 60 minutes, including 30 minutes of Tai Chi exercises and 15 minutes of warm-up and cold down. The control group will have 1 health lecture every month, 3 times in total 12 weeks. During the 12-week experiment, all participants will be asked to keep normal diet and daily routine.

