## **3.8 Data management and analysis**

### **3.8.1 Data management**

The research report form is filled in by the research object and the result evaluation personnel. The research report form consists of an activity log sheet, a blood lipid measurement sheet, a body composition measurement sheet, a physical fitness measurement sheet, and an adverse event record sheet. After the completed research report sheet is reviewed by the project manager, the data entry clerk is organized to enter the data and Unified management of the original table.

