### **3.9 Quality control**

1) Quality control of the informed consent of volunteers: Before signing the informed consent form, extensive education and communication should be carried out by the volunteer participants, so that the volunteers fully understand the content of the informed consent form.

2) Volunteer recruitment quality monitoring: strictly screen, all volunteers according to the inclusion and exclusion criteria.

3) Quality monitoring of random control and blind method: The project manager randomly grouped qualified subjects according to the number of the screener according to the random grouping sequence, properly kept the blind bottom, and unbind after the data analysis is over.

4) Quality control of the intervention process: The project manager supervises the coaching and training process of the coach, and the coach should supervise and guide the training process of the volunteers of the intervention group.

5) Quality monitoring of statistical analysis: The measurement data must be clearly filled in the research report form. Those whose results are zero and those that cannot be detected in the test should be indicated by corresponding symbols and cannot be vacated in order to distinguish them from missing values. If there is a missing value, look up

the original data, and fill it in for missing; if there is no record in the original data, notify the subject to recheck immediately; if the missing value affects the resulting judgment, the case is eliminated.

6) Data management quality control: The list of documents that the project manager must keep is checked one by one. If there are any missing items, the relevant personnel shall be required to fill in them.

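### Adverse-event incidence per group is the safety index, but contact is 36 sessions against 3 lectures and no common enquiry or recording at exit is stated, so the index is open to ascertainment bias of unknown direction

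*Protocol*

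**What the plan says.** Protocol 3.7.3 sets the only safety measure. On recording it says: "The side effects and adverse events that occurred during the study were recorded, and the reasons were analyzed". On the index it says: "The incidence of adverse events in each group was used as the evaluation index". The index is a percentage formed from "number of adverse events/total number of cases in this group".

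Protocol 3.5 sets the contact schedule. The two Tai Chi arms "will receive Tai Chi training 12 weeks, 3 times a week, each course is 60 minutes". For the third arm: "The control group will have 1 health lecture every month, 3 times in total 12 weeks". Under 3.9, item 4, "the coach should supervise and guide the training process of the volunteers of the intervention group"; no counterpart is given for controls.

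Protocol 3.8.1 puts an adverse-event sheet inside the research report form and says: "The research report form is filled in by the research object and the result evaluation personnel". Coaches are not mentioned there. Section 3.6 lists what is done at Visits 1 to 3 in all participants, and an adverse-event enquiry is not on the list.

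Among the exit criteria in 3.2.3, item 3 covers sudden illness or injury that prevents further training, and item 6 reads: "Those who have adverse events and are not suitable to continue practicing". The protocol does not say who records the event at that point, or whether the man is followed to week 12.

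**The concern.** An incidence by arm can be read across arms only if an event of a given kind has about the same chance of reaching the record in each. Here the opportunity differs by design. A man in a training arm meets a supervising coach three times a week, whereas a control has one scheduled contact a month. Without a question put to everyone at the same times, a minor complaint may be noted in one arm and go unmentioned in another.

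A second route runs the other way. The exit criteria on illness, injury and adverse events are worded around training and practising, so they bear mainly on the Tai Chi arms. If an event that leads to exit is not entered on the sheet, the training arms lose events that matter most for safety.

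At stake is whether the three percentages can be interpreted at all. Neither an apparent excess nor an apparent absence of events under Tai Chi could be separated from differences in how events were collected. This arises when the data are collected: an event that was never elicited cannot be recovered at analysis.

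**Working it through.** The protocol gives no adverse-event rate, capture probability or power for safety, so there is no stated safety figure to reproduce. Its only computed figure, 66 men for a one-way ANOVA on blood lipids, has no bearing here.

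**Inputs from the protocol.** 3 sessions a week for 12 weeks, and 3 lectures (3.5); three visits common to all arms (3.6); 30 men per arm (3.3); events divided by cases in the group (3.7.3).

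**Inputs assumed.** A true incidence of 20% in every arm (6 events in 30 men), and the capture probabilities and losses at exit used below.

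**1. Contacts.** Sessions: 12 × 3 = 36, against 3 lectures, a ratio of 36/3 = 12. With the three common visits: 39 against 6, a ratio of 6.5. These are ratios of opportunity, not of bias.

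**2. Unequal capture.** Observed incidence = true incidence × capture probability. With equal true incidence, the observed ratio is (capture in Tai Chi)/(capture in control), whatever the true rate.

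| Capture, Tai Chi | Capture, control | Observed, Tai Chi | Observed, control | Ratio |
|---|---|---|---|---|
| 90% | 90% | 18% | 18% | 1.0 |
| 90% | 60% | 18% | 12% | 1.5 |
| 90% | 45% | 18% | 9% | 2.0 |
| 90% | 30% | 18% | 6% | 3.0 |

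The first row is the case where every arm is asked alike: there is no distortion.

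**3. Events lost at exit.** Take a Tai Chi arm with 6 true events in 30 men, all otherwise captured.

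| Events lost | Over 30 men | If those men also leave the denominator |
|---|---|---|
| 0 | 6/30 = 20.0% | 6/30 = 20.0% |
| 2 | 4/30 = 13.3% | 4/28 = 14.3% |
| 3 | 3/30 = 10.0% | 3/27 = 11.1% |
| 6 | 0/30 = 0% | 0/24 = 0% |

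**4. Both together.** Suppose Tai Chi capture is 90% but a third of those events are lost at exit. Effective capture is 0.90 × 2/3 = 0.60. Against control capture of 60% the ratio is 0.60/0.60 = 1.0; against 90% it is 0.60/0.90 = 0.67; against 30% it is 0.60/0.30 = 2.0. The net direction depends on quantities that the protocol does not give.

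**5. Events over men.** The numerator counts events. Ten men with four events each give 40/30 = 133%, while 10/30 = 33% of men are affected. A recurring complaint may be entered more often where there are more occasions to mention it, so contact frequency can act on this index directly.

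**The case against.** The strongest reply is that the protocol does not show bias. Participants in all arms fill in the same report form, and nothing says that events are collected at sessions or by coaches. If every man completes the sheet on one schedule, 36 against 3 contacts need not matter. This stands: a reader might infer that the comparison **is** biased, or that Tai Chi events will be over-counted, and the document supports neither. What remains is that no such schedule is stated.

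A reader might also infer that events in men who leave are lost. The document does not say so. Section 3.7.3 covers events during the study without limiting them to completers, and exit for an adverse event presupposes that someone knows of it. The rule in 3.9 that eliminates a case concerns missing values, not exits. Loss is possible because recording at exit is not assigned to anyone; it is not established.

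No between-arm contrast or test is named for adverse events, and the objectives in section 2 concern fitness and blood lipids. A comparison is implied by a per-group index in a three-arm randomised trial, but only implied. It would be unfair to say that the trial fails a stated safety aim.

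The size rests wholly on assumptions. It would also be wrong to present 6 of 30 as the protocol's drop-out figure: section 3.3 takes 20% of 22, which is 4.4, rounded to 5, and does not link drop-out to adverse events.

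Finally, prompts and their timing may stand in a case report form or manual that is not shown. That limits the point to a clarification, but it belongs beside the index because later analysis cannot supply it.

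**Conclusion.** The point holds as a risk that the protocol leaves open. Four facts support it: the index is incidence by group; supervised contact is 36 sessions in the training arms against 3 lectures in control; no common enquiry is stated; and neither the coach's part in the adverse-event sheet nor recording at exit is stated. The per-group incidence is therefore open to ascertainment bias of unknown direction.

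Its size cannot be derived from the document. Under the assumed capture probabilities, and before any loss at exit, an observed ratio of 1.5 to 3.0 could appear with no true difference. Losing 3 of an assumed 6 events at exit would turn 20% into 10%. If all arms are asked alike and events at exit are recorded, the distortion from these two routes disappears.

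Safety is neither a primary nor a secondary outcome here, and the efficacy results are untouched. This is a worthwhile, inexpensive improvement that has to be made before data collection.

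**What to change.** In Protocol 3.7.3:

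- Ask every man in all three arms the same short adverse-event questions at matched monthly times (at the existing lecture for controls, at the matching session for the Tai Chi arms), at Visit 3, and at exit for anyone who leaves. The lecture weeks are not given, so tie the prompts to the lectures.
- Have coaches complete the adverse-event sheet for any event they see, and name them in 3.8.1.
- Keep all randomised men in the denominator, and report the number of men with at least one event beside the event count.
- Use the commonly prompted events for any comparison between arms. Report all recorded events, including those seen at sessions, alongside by arm. Restricting the report to prompted events could drop injuries that a coach witnessed and understate harm.

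The exit criteria themselves need no change for this purpose.

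The cost is a one-page question sheet, a telephone call to men who exit, and two safety tabulations instead of one. The monthly prompts and the Visit 3 enquiry use contacts that are already planned.

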#### **3.1.1 Randomization and allocation concealment**

The eligible participants will be randomly allocated in a 1:1:1 ratio to either the Bafa Wubu Tai Chi group, tradition He-styles Tai Chi group and control group. The random allocation sequence will be generated using web programming at <http://www.randomizer.org> by the project manager. The eligible participants will be informed of their allocation result by the project manager via telephone after their baseline information has been assessed.

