**Figure: 4 Sample size calculation.**

The total sample size is 66 persons. The sample size is 22 persons per each group.

$$\text{Drop out} = 20\% = 4.4 = 5$$

Therefore, the number of sample size of each group was 27 subjects. The sample size of this study is set to 30 persons per group. The purpose of this setting is to further improve the inspection performance (Power value). Substitute 30 samples per group into the G Power calculation program to derive a higher performance value (Power value). So each group will select 30 sample sizes.

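### The adverse-event incidence formula in section 3.7.3 divides events by persons, so it gives mean events per man × 100, not the percentage of men affected

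*Protocol*

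**What the plan says.** Section 3.7.3 (Safety indicators) has side effects and adverse events recorded and their causes examined. It then fixes one summary measure: "The incidence of adverse events in each group was used as the evaluation index". The formula is labelled "The incidence rate of adverse events", carries a percent sign, and is "number of adverse events/total number of cases in this group" multiplied by 100%. The section gives no other safety index.

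The protocol does not define a case in this formula. Section 3.9 uses the word for a participant, as in "if the missing value affects the resulting judgment, the case is eliminated". The denominator is therefore a number of people.

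Nowhere does the protocol say that a participant is counted once, that only first events count, or that person-time is used. Two other provisions bear on whether events can repeat in one man:

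- Section 3.5 gives the exercise groups "Tai Chi training 12 weeks, 3 times a week".
- The adverse-event exit criterion in section 3.2.3 covers "Those who have adverse events and are not suitable to continue practicing". A man who has an event and remains suitable does not exit under it.

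**The concern.** A percentage labelled as an incidence will normally be read as the share of participants who had the event. The stated formula does not give that share unless every affected man has exactly one event. Where events recur, the figure depends both on how many men are affected and on how often each is affected, and the two cannot be separated afterwards from the single number.

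Two things are at stake. The reported percentage can be far above the share of men harmed, and can be impossible as a percentage of people. The comparison between arms can also be misread. Section 2 makes comparing the two Tai Chi styles one of the study's two aims, and although that aim is worded for fitness and lipids, readers will compare the arms on safety too. One or two men with repeated minor complaints could make a style look worse than another in which more men were affected.

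This is not a detail left open for a statistical analysis plan. The protocol states the formula itself, and the formula does not yield the quantity it names.

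**Working it through.** **Plan's own figure.** The protocol gives no adverse-event count, rate or percentage, so there is nothing to reproduce. All event counts below are assumptions.

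**Inputs from the protocol**
- Index: events ÷ persons × 100% (section 3.7.3).
- Group size: 30 (section 3.3, "So each group will select 30 sample sizes"), with participants who "will be randomly allocated in a 1:1:1 ratio" (section 3.1.1).
- Exposure in an exercise arm: 12 weeks × 3 sessions = 36 sessions per man, and 36 × 30 = 1,080 per arm at full attendance (section 3.5).

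**Step 1: what the formula measures.** Let *E* be total events, *P* the men with at least one event, and *n* the men in the arm.
- Protocol index = 100 × *E*/*n*, which is mean events per man × 100.
- Share affected = 100 × *P*/*n*.
- Ratio of the two = *E*/*P*, the mean number of events per affected man. They agree only when *E* = *P*.

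**Step 2: when it exceeds 100%.** With *n* = 30, *E* = 30 gives 100% and *E* = 31 gives 31/30 = 103.3%. In an exercise arm, 31 events over 1,080 sessions is one event per 1,080/31 ≈ 35 sessions.

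**Step 3: can the order of the arms change?** Assumed counts, *n* = 30:

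| Assumed arm | Events | Men affected | Protocol index | Share affected |
|---|---|---|---|---|
| X: 2 men, 6 events each | 12 | 2 | 12/30 = 40.0% | 2/30 = 6.7% |
| Y: 8 men, 1 event each | 8 | 8 | 8/30 = 26.7% | 8/30 = 26.7% |
| Z: 3 men, with 12, 10 and 11 events | 33 | 3 | 33/30 = 110% | 3/30 = 10.0% |

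By the formula X looks worse than Y. By men affected Y is worse than X.

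**Step 4: how the gap depends on frequency and clustering.** For an assumed mean of *m* events per man, the expected index is 100*m*. The expected share affected is 1 − exp(−*m*) if events are Poisson, and 1 − (*k*/(*k* + *m*))^*k* if they cluster within men (negative binomial; smaller *k* means more clustering).

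| Mean *m* | Protocol index | Share affected, Poisson | Share affected, *k* = 1 / 0.5 / 0.25 |
|---|---|---|---|
| 0.1 | 10% | 9.5% | 9.1% / 8.7% / 8.1% |
| 0.5 | 50% | 39.3% | 33.3% / 29.3% / 24.0% |
| 1.2 | 120% | 69.9% | 54.5% / 45.8% / 35.6% |

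**Step 5: how often the order could flip.** Take one arm with mean 0.5 and *k* = 0.2 (expected share 1 − (0.2/0.7)^0.2 = 22%) and one Poisson arm with mean 0.35 (expected share 1 − exp(−0.35) = 30%). In 100,000 simulated trials with 30 men per arm, the two measures ranked the arms in opposite order in 37%. These arms were chosen so that their true rankings already differ on the two measures. The result shows that reversal can occur; it does not say how likely it is in this trial.

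**The case against.** The best defence is that events per person over a common 12 weeks is a legitimate measure, proportional to an event rate when follow-up is equal. That stands. The quantity is usable, and what is wrong is presenting it as a percentage incidence.

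The authors may have meant the number of participants with an event. That is possible, but the text does not say so, and anyone applying the formula as written would count events. Nor does the protocol say how events are counted: recurrent soreness might be logged as one continuing event, in which case the gap narrows. These are reasons to state the definition clearly.

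The effect may also be small. The men are 18 to 23 years old, and severe cardiovascular or musculoskeletal disease is excluded, so few events are plausible. Without recurrence the two measures are identical. Safety is neither a primary nor a secondary outcome, and the adverse event record sheet in section 3.8.1 probably allows participant-level counts to be recovered. All of this limits the consequence without making the formula right.

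Three stronger readings are tempting and are not supported:

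- **That the denominator shrinks.** A reader might infer this from the exit criteria and the elimination rule. Section 3.2.3 does not say that men who exit leave the safety denominator. The rule in section 3.9 concerns missing values in measurement data and is not applied to adverse events.
- **That a planned binomial interval or test is invalid.** Section 3.7.3 plans neither for adverse events. Section 3.8.2 names tests for continuous or ranked outcomes and does not apply its confidence intervals to adverse events.
- **That the arms will be misranked.** The examples show only that they can be.

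**Conclusion.** The point holds as a defect of definition. Followed as written, section 3.7.3 produces mean events per man × 100 under a label that readers will take as the percentage of men affected. The index overstates that percentage by a factor equal to the mean number of events per affected man. It has no ceiling at 100%, and it can put the arms in a different order.

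The size rests on assumptions, because the protocol gives no event rate. It is nil without recurrence, slight for rare events, and large where minor events recur in the same men: 50% against 24 to 39% at a mean of 0.5 events per man, over the clustering range examined. That repeats can occur follows from the 36 sessions and an exit criterion that does not remove every man who has an event.

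The efficacy analyses and the sample size are not touched. The correction is worth making because this is the only safety index stated and the change is simple.

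**What to change.** In section 3.7.3, replace the formula with: incidence (%) = number of participants with at least one adverse event ÷ number of participants randomised to that group × 100. Report the total number of adverse events in each group separately, as a count or as events per person, without a percent sign.

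Naming randomised participants makes the denominator explicit; it does not imply that the current wording removes anyone.

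The cost is one formula and one sentence. The adverse event record sheet should already hold what is needed, provided each entry can be traced to a participant. No visit, measurement, sample-size figure or clinical rule changes.
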